# Clinical research on the efficacy and safety of Bosinji for low back pain with radiculopathy caused by herniated intervertebral disc of the lumbar spine

**DOI:** 10.1097/MD.0000000000013684

**Published:** 2018-12-14

**Keywords:** bosinji, herbal medicine, low back pain, lumbar disc herniation, lumbar herniated intervertebral disc, radiculopathy

## Abstract

**Background::**

A lumbar herniated intervertebral disc (LHIVD) is a common problem that usually causes low back pain and radiating pain. The effectiveness of Bosinji, one of the herbal medicines used for low back pain and radiating pain in patient with LHIVD, has been reported in several studies; however, little clinical evidence is available owing to the methodological limitations in previous studies. Hence, the present study aims to establish the clinical evidence regarding the efficacy and safety of Bosinji in improving pain, function, and quality of life in LHIVD patients.

**Method/design::**

This is a multicenter, open-label, randomized, controlled, and equivalence trial with 2 parallel arms. A total of 74 patients who have low back pain and radiating pain due to LHIVD will be recruited and randomly allocated to the experimental group and control group. The patients in the experimental group and control group will take 2.5 g of Bosinji granule (1.523 g of Bosinji extract) or Loxonin tablet (60 mg of loxoprofen) 3 times a day for 6 weeks. Additionally, both groups will receive the same acupuncture treatment once a week for 6 weeks as a concurrent treatment. Changes in the 100-mm visual analogue scale (VAS) for low back pain after 6 weeks from baseline will be assessed as the primary outcome. Furthermore, the 100-mm VAS for radiating pain, Oswestry disability index (ODI), Roland–Morris disability questionnaire (RMDQ), EuroQol 5 Dimensions 5 Levels (EQ-5D-5L), global perceived effect (GPE), and deficiency syndrome of kidney index (DSKI) will be used to evaluate secondary outcomes. Outcomes will be assessed at baseline and at 3, 6, and 10 weeks after screening. For the safety evaluation, laboratory examinations including complete blood count, liver function test, renal function test, blood coagulation test, inflammation test, and urine analysis will be conducted before and after taking the medications.

**Discussion::**

The results of this trial will be used to establish clinical evidence regarding the use of Bosinji with acupuncture treatment in the treatment of patients with LHIVD.

**Trial registration number::**

NCT03386149 (clinicaltrials.gov) and KCT0002848 (Clinical Research Information Service of the Republic of Korea).

## Introduction

1

A lumbar herniated intervertebral disc (LHIVD) is defined as a medical condition that causes compression and irritation of the dural sac and nerve roots due to displacement of the intervertebral disc in the lumbar region.^[1]^ As low back pain and radiating pain, which are the most common symptoms of LHIVD, greatly affect the daily life and working status of patients, pain relief is a major concern in the conservative treatment of patients with LHIVD.^[2,3]^

Herbal medicines have been used clinically for the treatment of LHIVD mainly in Asian countries, and there have been a number of reports of evidence of their effectiveness.^[4,5]^ Bosinji, the commercial name of *Ucha-Shinki-hwan* (*Goshajinkigan* in Japanese), which consists of 10 crude drugs, is one of the herbal formulations traditionally used for low back pain with radiating pain.^[6]^

Each component of Bosinji has shown several pharmacological effects in experimental studies; these effects may explain the mechanism of its effect on LHIVD. *Aconitum carmichaelii* exerts an anti-nociceptive effect by stimulating spinal kappa-opioid receptors via release of dynorphin,^[7]^ as well as a blood flow-increasing effect by promoting the production of nitric oxide.^[8]^ Catalpol, an iridoid glucoside found in *Rehmannia glutinosa*, also has an anti-nociceptive effect associated with modulation of neuroinflammation in the spinal cord in rats.^[9]^ Other components of Bosinji such as *Corni officinalis*,^[10]^*Alisma orientale*,^[11]^*Poria cocos*,^[12]^*Paeonia suffruticosa*,^[13]^ and *Cinnamomum cassia*,^[14]^ show anti-inflammatory effects.

Experimental research has shown Bosinji to be possessing properties similar to those of its individual components. Similar to *Aconitum carmichaelii*, Bosinji has an anti-nociceptive effect that involves the activation of kappa-opioid receptors, thereby reducing paresthesia,^[15]^ as well as vasodilating effect via increase in nitric oxide production.^[16]^ Nakanishi et al have reported that Bosinji suppresses the expression of tumor necrosis factor-α,^[17]^ which is a critical molecular mediator in the pathogenesis of radiating pain.^[1]^

Based on the mechanisms revealed in experimental studies, Bosinji have also been shown to be clinically effective in the treatment of LHIVD in observational studies.^[18,19]^ One randomized controlled trial (RCT) reported that the effectiveness of Bosinji was similar to that of nonsteroidal anti-inflammatory drugs (NSAIDs) for low back pain and paresthesia in the lower extremities; however, this trial carried many unclear risks of bias and methodological limitations, and hence, a definite conclusion could not be arrived at.^[20]^

For the clinical application of Bosinji in treating low back pain with radiating pain caused by LHIVD, reliable evidence from pragmatic RCT reflecting the actual clinical situation in Korean medical clinics where herbal medicine treatment is conducted with acupuncture treatment concurrently^[21]^ is required. Therefore, we will evaluate the equivalence of Bosinji to NSAIDs in concurrent with acupuncture using a rigorously designed, full-scale RCT protocol that includes assessments on pain, function, quality of life (QoL), and safety.

## Methods

2

### Trial design

2.1

This study is a multicenter, open-label, randomized, controlled, and equivalence trial with 2 parallel arms (1:1 ratio). The trial will be conducted at the Kyung Hee University Hospital at Gangdong (KHUHGD), Kyung Hee University Medical Center (KHUMC), Dongguk University Bundang Oriental Hospital (DUBOH), and Daegu Korean Medicine Hospital of Daegu Haany University (DKMHDHU). The efficacy and safety of Bosinji in patients with low back pain with radiculopathy due to LHIVD will be evaluated by comparison with loxoprofen, one of the NSAIDs.

This protocol has been approved by the Institutional Review Boards (IRBs) of the institutions (KHUHGD: KHNMCOH 2017-08-002, KHUMC: 170918-HR-039, DUBOH: 2017-0007, and DKMHDHU: DHUMC-D-17019). The trial has also been registered at clinicaltrials.gov, which is a website of the United States National Institutes of Health (registration number: NCT03386149), as well as in the Clinical Research Information Service of the Republic of Korea (registration number: KCT0002848). All research procedures comply with Korean Good Clinical Practice (KGCP) and the Declaration of Helsinki. The methodology was established in accordance with the Standard Protocol Items: Recommendation for Interventional Trials (SPIRIT)^[22]^ and with the revised Standards for Reporting Interventions in Clinical Trials of Acupuncture (STRICTA).^[23]^

### Participants

2.2

The inclusion criteria for this study are as follows: age over 19 years; radiating pain consistent with abnormalities in the lumbar spine that are more severe than bulging, as shown on computerized tomography (CT) or magnetic resonance imaging (MRI)^[24,25]^; low back pain score between 40 and 80 points on the 100-mm pain visual analogue scale (VAS); and voluntary participation and provision of a signed informed consent form after a detailed explanation of the clinical trial has been provided.

Participants who have the following characteristics will be excluded:

1.congenital abnormalities or surgical history in the lumbar region;2.red flag signs that may indicate cauda equina syndrome, such as bladder and bowel dysfunction or saddle anesthesia;3.tumor, fracture, or infection in the lumbar region;4.injection in the lumbar region within 1 week of the screening;5.psychiatric disorder currently being treated, such as depression or schizophrenia;6.liver function abnormality (aspartate transaminase [AST] or alanine transaminase [ALT] >100 U/L for men/70 U/L for women);7.renal function abnormality (serum creatinine >2.0 mg/dL);8.other diseases that could affect or interfere with therapeutic outcomes, including severe gastrointestinal disease, cardiovascular disease, hypertension, diabetes, renal disease, liver disease, or thyroid disorder;9.contraindications for NSAIDs, including concurrent disease, hypersensitivity reaction, or other medication;10.conditions for which acupuncture is contraindicated, for example, skin disease or hemostatic disorder (international normalized ratio >2.0 or taking anticoagulant);11.pregnancy, breastfeeding or having pregnancy plans;12.other condition for which herbal medicine treatment is contraindicated; and13.participation in other clinical trials within 1 month of the screening.

### Procedure

2.3

A total of 74 participants with LHIVD will be recruited at four institutions, each of which will recruit an appointed number of patients (KHUHGD: 20, KHUMC: 18, DUBOH: 18, and DKMHDHU: 18). All participants who can read and write in Korean will be informed that they may voluntarily participate and that they can withdraw their consent at any stage. They will also be given essential information regarding the study protocol, including purpose, selection of participants, interventions by random allocation, schedule, expected benefits and risks, alternative treatment options, and confidentiality. Those who agree and sign the informed consent form will be screened through the assessment of demographics, medical history, present illness, vital sign, pregnancy test, and laboratory test. If they meet the eligibility criteria, the participants will be randomly allocated to the experimental group or control group. After random allocation, the assigned group will undergo a 6-week treatment, and assessment of outcome measure will be performed at 3, 6, and 10 weeks later according to schedule (Fig. 1).

**Figure 1 F1:**
[figure not shown]
Standard Protocol Items: Recommendations for Interventional Trials (SPIRIT) figure.

### Interventions

2.4

In the experimental group, 2.5 g of Bosinji granule (1.523 g of Bonsinji extract, Tsumura Co., Tokyo, Japan) will be orally administered 3 times a day at 30 minutes after every meal for 6 weeks. Bonsinji extract comprises a mixture of extract from the following 10 crude drugs in fixed proportions (Table 1). Bosinji is manufactured by Tsumura Co. in compliance with Good Manufacturing Practice standards. In the preparation phase, each crude drug undergoes macroscopic and microscopic examination. The extract and its components are also subjected to physicochemical tests. Bosinji granule is produced by a process involving decoction, separation, concentration, drying, and granulation. To ensure consistency and safety, multiple quality tests, including quantitative analysis of the components, microbial limits test, and residual pesticides test, are performed.

**Table 1 T1:**
[figure not shown]
Composition of Bosinji extract.

In the control group, Loxonin tablet (60 mg of loxoprofen, Dong Wha Pharm Co., Ltd, Seoul, Korea) will be orally administered 3 times a day at 30 minutes after each meal for 6 weeks. Three weeks of medication will be provided at week 0 and week 3, and the remaining medication will be withdrawn to confirm the medication compliance.

### Concurrent treatment

2.5

As a concurrent treatment, an identical acupuncture treatment will be conducted once a week for all participants regardless of group during the medication period. Acupuncture treatment will be performed on 20 predefined acupoints using 40 mm x 0.25 mm acupuncture needles according to STRICTA (Table 2). The selection of acupoints and details of the procedure have been modified from similar studies^[26,27]^ by a committee of Korean medical doctors (KMDs) experienced in LHIVD and acupuncture. Acupuncture treatment will be performed by KMDs who have completed or have been taking a specialist acupuncture and moxibustion course for at least 3 years. To maintain homogeneity of treatment among the participating centers, all practitioners will undertake a training course together in advance.

**Table 2 T2:**
[figure not shown]
Details of acupuncture treatment using the STRICTA 2010 checklist.

### Outcomes

2.6

All assessments will be performed according to schedule by blinded independent researchers who are not involved in the intervention. The primary outcome will be a change in VAS for low back pain. The secondary outcomes will be evaluated using the VAS for radiating pain, Oswestry disability index (ODI), Roland-Morris disability questionnaire (RMDQ), EuroQol 5 Dimensions 5 Levels (EQ-5D-5L), global perceived effect (GPE), and deficiency syndrome of kidney index (DSKI). Additionally, all adverse events will be recorded at each visit.

#### Primary outcome measure

2.6.1

##### 100-mm VAS for low back pain

2.6.1.1

The intensity of low back pain will be evaluated using the 100-mm VAS at pre-trial screening and at weeks 0 (baseline), 3, 6 (primary endpoint), and 10 (follow-up sessions).^[28]^ Participants will be asked to record their pain intensity within the past week on a 100-mm linear scale (0, absence of pain; 100, worst pain imaginable). Changes from baseline after 6 weeks of treatment will be compared between the groups as the primary outcome.

#### Secondary outcome measures

2.6.2

##### 100-mm VAS for radiating pain

2.6.2.1

The intensity of radiating pain in the lower extremities will also be assessed using a 100-mm VAS at pre-trial screening and at weeks 0, 3, 6, and 10. Participants will be asked to record their pain intensity within the past week on a 100-mm linear scale (0, absence of pain; 100, worst pain imaginable).

##### Oswestry disability index (ODI)

2.6.2.2

Inability to function in daily life due to low back pain will be assessed using the ODI at weeks 0, 3, 6, and 10. The ODI questionnaire consists of 10 sections: pain, personal care, lifting, walking, sitting, standing, sleeping, sex life, social life, and traveling. Each question is scored from 0 to 5, and the total score is calculated as a percentage disability.^[29]^

##### Roland-Morris disability questionnaire (RMDQ)

2.6.2.3

Physical disability due to low back pain will be assessed using the RMDQ at weeks 0, 3, 6, and 10. The RMDQ contains 24 sentences describing the discomfort that may occur with low back pain. Participants will need to check the sentences that would best describe their life on that day, and the score is based on the total number of sentences checked (from 0 to 24).^[30]^

##### EuroQol 5 Dimensions 5 Levels (EQ-5D-5L)

2.6.2.4

The QoL and general health status will be assessed using the EQ-5D-5L at weeks 0, 3, 6, and 10. The EQ-5D-5L consists of the EQ-5D descriptive system and EQ-VAS. The EQ-5D descriptive system assesses the following five dimensions: mobility, self-care, usual activities, pain/discomfort, and anxiety/depression. Each dimension is rated from 1 to 5 (1, no problem; 2, slight problems; 3, moderate problems; 4, severe problems; and 5, extreme problems). The EQ-VAS scale can be used to assess a patient's current health status. It is a 20-cm scale numbered from 0 to 100 (0, the worst health they can imagine; 100, the best health they can imagine).^[31]^

##### Global perceived effect (GPE)

2.6.2.5

The subjective change of symptom will be assessed using the GPE at weeks 3, 6, and 10. The participants will score their perceived change after treatment using a 7-point scale (1, worst ever; 2, much worse; 3, worse; 4, not improved and not worse; 5, slightly improved; 6, much improved; and 7, best ever).^[32]^

##### Deficiency syndrome of kidney index (DSKI)

2.6.2.6

The deficiency syndrome of kidney (DSK), a concept of the Korean medical diagnosis system, will be assessed using DSKI at weeks 0 and 6. The DSKI shows the severity of the DSK by scoring the 12 DSK-related symptoms from 0 to 2 points (1, no symptom; 2, moderate; and 3, severe).^[33]^

### Safety

2.7

To confirm the safety of the medications, the following laboratory tests will be carried out at the pre-screening point and at week 6 when the medication treatment is completed; complete blood count (white blood cells, red blood cells, hemoglobin, hematocrit, and platelet), liver function test (total protein, albumin, AST, ALT, alkaline phosphatase, total bilirubin, and γ-glutamyl transferase), renal function test (uric acid, blood urea nitrogen [BUN], and creatinine), fasting plasma glucose, prothrombin time, activated partial thromboplastin time, erythrocyte sedimentation rate, C-reactive protein, and urine analysis (color, specific gravity, pH, protein, glucose, ketone, urobilinogen, bilirubin, nitrite, blood, and white blood cell). Additionally, AST, ALT, BUN, and creatinine will be examined at week 3. For women of childbearing potential, a urine human chorionic gonadotropin test will be performed using a stick-type pregnancy tester, and they will be educated about the need for medically acceptable contraception during the study period.

At each visit, the researchers will measure the vital signs, such as blood pressure, pulse rate, and body temperature and collect information about the occurrence of adverse event (AE) and changes in the drug being taken. Information about expected AEs, as well as a contact number, will be given to the participants along with the informed consent form before the pre-trial screening. If AEs do occur, the principal investigator will evaluate the severity of the incident, as well as its relation to the interventions, and provide proper examination and treatment in accordance with the compensation rules. The progress of all AEs will be recorded in the case report form (CRF) and handled in accordance with the standard operation protocol (SOP) of the IRB and the regulation of KGCP.

### Sample size

2.8

The sample size was calculated based on a previous similar study (assuming σ = 9.18, 
[figure not shown]
 = 10),^[20]^ and the equivalence margin for the primary outcome was set at 18.^[34]^ With a 0.05 significance level, 80% power, and 1:1 ratio, we calculated the adequate sample size using the following formula:
 

Finally, we determined that the sample size required in each group should be 37 participants by considering the dropout rate (20%) and medication compliance rate (95%) on the calculated value. The 74 participants will be recruited separately at the four research sites; each site will recruit the following numbers of participants: KHUHGD: 20, KHUMC: 18, DUBOH: 18, and DKMHDHU: 18.

### Randomization and allocation concealment

2.9

A total of 74 participants will be randomly allocated to the experimental group or control group according to a block randomization procedure with a 1:1 ratio after stratifying them by institutions. The randomization sequence will be generated by an independent statistician using the package “blockrand” 1.3 of R (The R Foundation for Statistical Computing, Vienna, Austria). For allocation concealment, sealed, opaque envelopes containing random code will be sent to each institution. The clinical research coordinator will open the envelope and allocate participants to their groups after screening.

### Blinding

2.10

The medications used in this study are in the form of tablets and granules and can easily be distinguished visually. Therefore, because it is impossible to achieve patient blinding, this research was designed as an open-label study. However, for objective analysis, evaluators and statisticians do not provide information on group assignments.

### Statistical methods

2.11

The data will be corrected using the “last observation carried forward” method and then analyzed using the “intention-to-treat” principle. The independent *t* test and Chi-square test will be used to compare the differences in general characteristics between groups. As a primary outcome, changes in the 100-mm VAS for low back pain from baseline to the end of the end of the medication treatment will be compared between groups using an independent *t* test. Equivalence will be evaluated based on the equivalence margin of 18 mm and 95% confidence interval (CI). To compare the outcomes of each session with the baseline values, an analysis of covariance will be used. Trends over time and time-by-treatment interactions will be analyzed using a repeated measures analysis of variance. All statistical analyses will be performed using PASW statistics 18 for Windows, and the statistical significance level will be set at .05.

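### Carrying the last VAS value forward can bias the week-6 difference either way, and under similar dropout with a growing effect it favours a false claim of equivalence

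*Protocol article*

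**What the plan says.** The Trial design section describes a "multicenter, open-label, randomized, controlled, and equivalence trial with 2 parallel arms (1:1 ratio"). The primary outcome is the change in low back pain VAS from baseline to week 6. The VAS is recorded at screening and at weeks 0, 3, 6 and 10 (100-mm VAS for low back pain, 2.6.1.1).

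On missing data, Statistical methods (2.11) states one rule: "The data will be corrected using the “last observation carried forward” method and then analyzed using the “intention-to-treat” principle". The same section compares the changes by an independent t test and judges equivalence by a 95% CI against 18 mm.

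The Sample size section (2.8) reaches 37 per group by "considering the dropout rate (20%) and medication compliance rate (95%) on the calculated value". It does not say when in the trial the dropout is expected.

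**The concern.** Only two values can be carried to week 6. A patient lost before week 3 has nothing but the baseline, so the week-6 change is set to exactly 0 mm. A patient lost between weeks 3 and 6 keeps the week-3 change. Neither is an estimate of the week-6 outcome, yet the t test treats both as observed.

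In an equivalence trial the error to guard against is declaring equivalence when the true difference is at or beyond the margin. A 95% CI held inside ±18 mm is meant to keep that error at 2.5% per side. If the filled values bring the arm means closer than they really are, the error rises, and the argument that this imputation is conservative, familiar from superiority trials, works in reverse. The article fixes this method for the primary analysis, so the point is about a choice that was made, not about detail left to an analysis plan.

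**Working it through.** **Inputs from the article.** Margin: "the equivalence margin for the primary outcome was set at 18" (mm). SD: "assuming σ = 9.18". Significance level 0.05, power 80%, 1:1 allocation, 20% dropout, 95% compliance, 37 per group. The symbol in front of the value 10 was lost in text extraction. It is read here as the expected difference because that reading reproduces the stated sample size.

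**The plan's own figure.** For two-sided equivalence of means:

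n = 2 × [SD × (z0.975 + z0.90) / (margin − difference)]² = 2 × [9.18 × (1.960 + 1.282) / (18 − 10)]² = 27.67, so 28.

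28 / (0.80 × 0.95) = 36.84, so 37. The stated figure reproduces.

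**Assumptions not in the article.** The true week-6 difference is exactly 18 mm, so every declaration of equivalence is false. The control arm improves by 35 mm and the experimental arm by 17 mm, or by 20 mm and 2 mm. Dropout is unrelated to outcome. The week-3 to week-6 correlation is 0.5. SDs of 20 and 25 are tried beside 9.18.

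**Expected difference after filling, 20% dropout in each arm.** Formula: 0.80 × 18 + (share lost after week 3) × (week-3 difference) + (share lost before week 3) × 0.

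- All lost before week 3: 0.80 × 18 = 14.4 mm.
- Half before, half after, week-3 difference 10: 14.4 + 0.10 × 10 = 15.4 mm.
- All after, week-3 difference 9 (half the final one): 14.4 + 0.20 × 9 = 16.2 mm.
- All after, week-3 difference 18: 14.4 + 0.20 × 18 = 18.0 mm.
- All after, week-3 difference 22: 14.4 + 0.20 × 22 = 18.8 mm.

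**Simulated false equivalence** (37 per arm, pooled 95% CI inside ±18, 40,000 runs per case, control improvement 35 mm, nominal 2.5%):

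| Case, 20% equal dropout | SD 9.18 | SD 20 |
|---|---|---|
| All before week 3 | 17.7% | 10.8% |
| Half and half, week-3 difference 10 | 13.2% | 7.6% |
| All after, week-3 difference 9 | 10.1% | 5.7% |
| All after, week-3 difference 18 | 2.5% | 2.5% |
| All after, week-3 difference 22 | 1.0% | 1.8% |
| Observed week-6 data only, any case | 2.4-2.5% | 2.4-2.6% |

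**Hand check of the first row at SD 9.18.** With 20% zeros, the variance in an arm is 0.80 × SD² + 0.80 × 0.20 × mean².

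- Control: 0.80 × 84.27 + 0.16 × 35² = 67.4 + 196.0 = 263.4.
- Experimental: 67.4 + 0.16 × 17² = 113.7.
- Standard error: √((263.4 + 113.7) / 37) = 3.19.
- False equivalence ≈ Φ((18 − 14.4) / 3.19 − 1.99) = Φ(−0.87), about 19%, close to the simulated 17.7%.

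With changes of 20 and 2 mm the variances are 131.4 and 68.1, the standard error is 2.32, and Φ(3.6 / 2.32 − 1.99) is about 33%. So the size of the arm changes matters as well as their difference.

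**Ranges over control improvements of 20-35 mm.**

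- 20% dropout, SD 9.18: 18-34% when carried from baseline, and 10-12% when carried from week 3 at half effect.
- 20% dropout, SD 20-25: about 9-13% and about 5-6% respectively.
- 20% dropout, week 3 already at 80% of the effect: about 5% at SD 9.18 and about 3.5% at SD 20.
- 10% dropout: about 3-12% across these cases.

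**Unequal dropout before week 3, 30% versus 10%, SD 9.18.**

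- Heavier in the worse arm: 0.9 × 35 − 0.7 × 17 = 31.5 − 11.9 = 19.6 mm, false equivalence 0.4-0.5%.
- Heavier in the better arm: 0.7 × 35 − 0.9 × 17 = 24.5 − 15.3 = 9.2 mm, false equivalence about 74%.
- No true difference, both arms improving by 30 mm: 0.9 × 30 − 0.7 × 30 = 6 mm, a difference that the filling alone creates.

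**The case against.** A reader might infer that carrying values forward shrinks any real difference and so always helps the equivalence claim. The article does not support that. The bias vanishes if the week-3 difference already equals the week-6 one, and it reverses if the difference narrows after week 3 or if dropout is heavier in the worse arm. The trial is open-label with products that patients can tell apart, so equal dropout cannot be taken for granted. This part of the objection stands in full.

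The largest figures also need a special combination: true difference at the margin, all 20% lost before week 3, equal dropout, SD 9.18, and an experimental arm that hardly improves. The article gives neither the arm changes nor the dropout timing, and a larger SD lowers the rates. The 20% is a planning allowance. Follow-up runs to week 10, and patients lost after week 6 still supply the primary endpoint, so 20% missing at week 6 is an upper reading. This stands too, and is why ranges are given.

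A further inference might be that the statement "Trends over time and time-by-treatment interactions will be analyzed using a repeated measures analysis of variance" is part of the same error. It concerns trends over time, not the equivalence decision, and is not faulted here. Nor is the lack of sensitivity analyses, which an analysis plan may hold.

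None of this defends the method. A rule whose bias depends on unknown dropout by arm and timing cannot be relied on to hold 2.5% per side.

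**Conclusion.** The point holds as a direction-dependent bias in the primary analysis. In the common situation of similar dropout in both arms and an effect still growing after week 3, the rule favours a false claim of equivalence.

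At a true difference of 18 mm with 20% equal, non-informative dropout before week 6, the error is about 10-34% at SD 9.18 for half-effect or baseline carry, and about 5-13% at SD 20-25. It is about 3-5% if week 3 shows 80% of the effect, and there is no inflation if the week-3 difference equals week 6. Unequal dropout of 30% versus 10% takes it anywhere from 0.4% to 74%.

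The margin, planning SD, group size and 20% allowance are the article's. Arm changes, dropout timing and balance, and the larger SDs are assumptions. The observed-data analysis keeps 2.5% only because dropout was assumed unrelated to outcome.

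**What to change.** In Statistical methods, replace carrying forward in the primary analysis with a likelihood-based mixed model for repeated measures on the low back pain VAS visits already collected, adjusted for baseline VAS and site. Estimate the treatment contrast at week 6 and compare its 95% CI with ±18 mm. Keep the carried-forward analysis as a sensitivity analysis only.

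The mixed model was not itself simulated here, and it relies on dropout being explained by the observed data. A tipping-point analysis that shifts imputed values against equivalence would probe that assumption. It is optional and can be left to the analysis plan.

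The cost is a change of wording, slightly more analysis work, and usually a somewhat wider CI. No extra visits or data are needed.

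### If Bosinji is truly worse than loxoprofen, the stated intention-to-treat/LOCF equivalence rule favours the claim; require a per-protocol set to agree

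*Protocol article*

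**What the plan says.** Section 2.11 of the protocol article fixes the data handling and the analysis principle in one sentence: "The data will be corrected using the “last observation carried forward” method and then analyzed using the “intention-to-treat” principle". The decision rule follows ("Equivalence will be evaluated based on the equivalence margin of 18 mm and 95% confidence interval (CI"). No second analysis set is named there or elsewhere in the article.

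The aim has two sides, both in the Introduction. One is pragmatic: a "pragmatic RCT reflecting the actual clinical situation in Korean medical clinics". The other is a statement about the drug: "we will evaluate the equivalence of Bosinji to NSAIDs in concurrent with acupuncture".

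Four other places bear on the point:
- Section 2.10 (Blinding): "because it is impossible to achieve patient blinding, this research was designed as an open-label study".
- Section 2.8 (Sample size) reaches 37 per group "by considering the dropout rate (20%) and medication compliance rate (95%) on the calculated value".
- Section 2.4 (Interventions) has tablets and granules returned: "the remaining medication will be withdrawn to confirm the medication compliance".
- Section 2.7 (Safety) has researchers at each visit "collect information about the occurrence of adverse event (AE) and changes in the drug being taken".

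So adherence and added drugs are both recorded, but the equivalence rule uses neither.

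**The concern.** In a superiority trial, anything that blurs the contrast between arms usually works against the claim. In an equivalence trial with a real difference between the drugs, it works for the claim. Three routes exist here:
- **Added NSAIDs.** A Bosinji patient who is still in pain knows what he or she is taking and may add a drug of the comparator's class. Intention-to-treat keeps that week-6 score. A ban in the full protocol would not remove the problem, because patients who break it are kept too.
- **Non-compliance.** Loxoprofen patients who stop taking the drug lose some of any advantage it has.
- **LOCF.** A patient lost before week 6 contributes a week-3 or baseline value. If the drugs separate gradually, that value shows less than the full difference.

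At stake is the trial's main claim: a true deficit at or near the margin could be reported as equivalence.

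**Working it through.** **Reproducing the plan's figure.** From section 2.8: SD 9.18, margin 18, significance level 0.05, power 80%, dropout 20%, compliance 95%. The symbol in front of the value 10 was lost in extraction; I read it as the assumed true difference. The printed formula is also lost, so I use the usual one:

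n = 2 × SD² × (z₀.₉₇₅ + z₀.₉₀)² / (margin − difference)² = 2 × 9.18² × (1.96 + 1.2816)² / (18 − 10)² = 27.7, so 28.

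28 / 0.80 / 0.95 = 36.8, so 37. The stated 37 per group reproduces, and 37 × 0.80 × 0.95 = 28.1 compliant completers per arm would be left.

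**Assumptions the documents do not supply.** A true deficit of exactly 18 mm; the share p of Bosinji patients who add an NSAID; the share r of the deficit they recover; SD 20 as an alternative to 9.18; Bosinji mean improvement of 12 mm at week 6; half of each arm's improvement reached by week 3; week-3/week-6 correlation 0.6; use starting after week 3. With that timing a user has three weeks on the NSAID, and three weeks of loxoprofen yields half its effect in the same model. So r = 0.5 is the coherent value.

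**Added NSAID use, closed form.** The mean difference becomes 18 × (1 − p × r), and the Bosinji arm gains variance (18r)² × p(1 − p). For p = 0.2, r = 0.5, SD 9.18:
- difference: 18 × 0.9 = 16.2 mm
- added variance: 81 × 0.16 = 12.96
- SE: √[(84.27 + 12.96 + 84.27)/37] = 2.215
- (18 − 16.2)/2.215 − 1.993 = −1.18, a probability of about 12%

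**Simulation** (40,000 trials per cell, 37 per arm, pooled 95% t-interval inside ±18 mm, random users, r = 0.5). False equivalence at a true 18 mm deficit:

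| Use in Bosinji arm | SD 9.18 | SD 20 |
|---|---|---|
| 0% | 2.5% | 2.5% |
| 10% | 6% | 4% |
| 20% | 12% | 6% |
| 30% | 22% | 8% |

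At a true deficit of 20 mm with SD 9.18, the same use rates give about 1%, 2.5% and 6%.

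**LOCF alone.** Take the plan's 20% dropout, all after week 3, at random and in both arms, with no added NSAID. The expected difference is 0.8 × 18 + 0.2 × 9 = 16.2 mm, inside the margin. Mixing week-3 and week-6 values adds variance of 6² × 0.16 = 5.76 (Bosinji) and 15² × 0.16 = 36 (loxoprofen). SE = √[(84.27 + 5.76 + 84.27 + 36)/37] = 2.384, and 1.8/2.384 − 1.993 = −1.24, about 11%. With SD 20 the simulated figure is about 6%.

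**What a second set does.** Claiming equivalence only if the per-protocol set also passes brings 12% (20% random users, SD 9.18) back to 2.5%. If the users are instead the worst 20% of the Bosinji arm at week 3, it only moves 14% to 11%.

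**The case against.** The strongest reply is that a condensed article need not list every analysis set, and that intention-to-treat suits a pragmatic trial. Both parts carry weight. A reader might infer that the trial has no per-protocol analysis at all. The article does not support that, since a fuller plan may contain one. But section 2.11 is not silent on the decision: it states the rule for claiming equivalence, and that rule is what is questioned. The pragmatic aim is a reason to keep intention-to-treat. It does not settle the statement about the drug, which added NSAID use would blur.

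The second reply concerns direction. A reader might infer that intention-to-treat always favours equivalence. It does so only under a true deficit. If the drugs are equal and an added NSAID gives extra relief in one arm, the difference moves away from zero. LOCF, too, can bias either way, depending on who leaves and when.

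The third concerns size. If users recovered the whole deficit, the 20% and 30% use figures at SD 9.18 would be about 30% and 56%. A reader might take these as the risk. They conflict with use that starts after week 3, and section 3 (Discussion) itself calls NSAID benefit in this condition controversial.

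The fourth is that inflating for compliance does not commit the plan to a per-protocol test. That stands: the 28 compliant completers show only that such a test is affordable.

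Finally, per-protocol exclusion can itself favour Bosinji by removing its poor responders. This also stands, and it is why the fix needs a sensitivity analysis.

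**Conclusion.** The concern holds conditionally. As stated, the equivalence rule is not conservative when Bosinji is truly worse than loxoprofen. With half recovery among users, the 2.5% error at an 18 mm deficit becomes about 6% to 22% over 10% to 30% use with SD 9.18, or 4% to 8% with SD 20. The plan's own 20% dropout under LOCF gives about 11% or 6% if half the effect is present by week 3. Use rates, recovery, timing and SD 20 are assumptions, and the risk shrinks as the deficit moves beyond the margin.

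The documents do not show that these rates will occur, that intention-to-treat is the wrong primary set, or that the sample size is wrong. The change should be made because the rule bears on the trial's main claim and the remedy uses data already collected. Confidence is medium, because the size is uncertain and a fuller plan may already cover part of it.

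**What to change.** Keep the intention-to-treat analysis and add to section 2.11:

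> A per-protocol equivalence analysis will exclude, in both arms, patients who used a non-study analgesic or lumbar injection before the week-6 assessment, patients non-compliant by returned medication at a threshold fixed in advance, and patients without a week-6 VAS. Equivalence will be claimed only if the 95% CI lies within ±18 mm in both the intention-to-treat and per-protocol sets. The number of users per arm will be reported. As a sensitivity analysis, not a condition for the claim, each VAS given after such use will be replaced by the last VAS before it.

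If the full plan already has a per-protocol equivalence analysis, it is enough to state in 2.11 that both sets must agree and to add the sensitivity analysis.

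The cost is one further analysis and some power; no new data or patients are needed. With about 28 per arm in the per-protocol set:
- **True difference 10 mm, SD 9.18:** SE = 9.18 × √(2/28) = 2.453, and (18 − 10)/2.453 − 2.005 = 1.26, so about 89%. With 20% random use in the Bosinji arm it is 85%. Both exceed the planned 80%.
- **No true difference, SD 20:** about 80% with no added use, against 94% for intention-to-treat alone with 37 per arm. With 20% use it falls to 73% (random users) or 66% (worst responders). This is the real downside if the SD is much larger than planned and added use is common.
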